### **Inclusion criteria**

1. Aged 18 years and above

2. Willing and able to provide informed consent (written/thumbprint/verbal)

#### **Exclusion criteria**

1. Have tested positive for COVID-19 and are still within the isolation period
2. Have a medical contraindication to nasal swabs (e.g., bleeding disorders, recent facial trauma).
3. Are unable to provide informed consent

#### **Main analysis**

A programmatic evaluation and analysis of data will report on the proportion of participants accepting to be tested, tested positive and those linking to care and treatment. A descriptive process evaluation will analyze month-by-month the numbers of COVID-19 tests conducted at each facility before introducing COVID-19 Ag-RDTs. Once Ag-RDTs are made available, numbers accepting the test, and numbers diagnosed Ag-RDT+ve will be collected. Denominators will be all clinic attendees.

Time trend analysis will be used for descriptive analysis of trends in numbers (%) of all attendees screened for symptoms, reporting one or more COVID-19 symptom, identified, and tested for COVID-19, and the number/percentage of those testing positive. Data will be reported for all patients, and for all patients who would be eligible for antiviral treatment if tested positive.

Descriptive analysis of the proportion of participants and binomial exact 95% CI accepting to test, testing positive and accepting next steps for COVID-19. The proportions will be stratified and compared either using t-test or Chi-square test for continuous and categorical variables accordingly.

#### **Ethical considerations for the OPD model use case**

Eligible participants will be given detailed information about the study and will be invited to participate (NC08A). Written informed consent will be obtained before study procedures commence. Written informed consent also explicitly covers the potential for subsampling for the process evaluation explaining that clients may be selected to be asked some additional questions about their experiences of the testing which means that the interviews could take up to 1hour.

In addition, written informed consent will be obtained from participants subsampled to take part in the patient cost exercise (NC09), as well as written informed consent from the providers sampled to take part in the provider cost exercise (NC10). If participants are illiterate, participant information sheets will be read to participants and thumbprint consent, alongside witness signature will be taken.

#### **5.1.3. Written informed consent will also be obtained from the study providers for the 2 qualitative interviews (NC03). Investigating potential COVID-19 outbreaks in congregate, populated settings**

##### **Objective**

We wish to evaluate the acceptability of professional use Ag RDT and use of KN95 masks by the COVID-19 positive participant to prevent infection of contacts in congregate settings (universities, workplaces) within the catchment area of the PCI facilities in Blantyre **to expand peak-testing capacity** during outbreaks and to facilitate early detection and enable effective infection prevention and control, including linkage to appropriate care.

##### **Outcome**

The primary outcome is the proportion accepting to be tested for COVID-19.

Secondary outcomes include an assessment of risk factors including vaccination history, socio-demographics and knowledge, attitudes, perceptions, and practices relating to COVID-19 transmission and prevention.

## **Overview**

An outbreak is defined as the occurrence of  $\geq 1$  new confirmed case in any congregate setting. We will actively work with district-wide COVID-19 response teams to get weekly reports of any such new cases.

Criteria for selecting a congregate setting for implementation of screening:

1. A working relationship must exist between the potential congregate setting and the district response team.
2. Must be one of the two below:
  - a. a university
  - b. a workplace
3. A gatekeeper must provide consent at institutional level for the implementation of screening.

We will select at most 5 congregate settings aiming to offer screening to ~323 participants (i.e. aiming to recruit a total of 323 participants across all 5 settings). Assuming that there would be at most two waves during study implementation period then two outreach screening activities would be conducted.

Professional Ag-RDT will be used with national guidelines followed for confirmation as well as linkage to care.

Suspected outbreaks of COVID-19 will be investigated among individuals in heavily populated environments in Blantyre such as universities and workplaces to facilitate early detection and enable effective infection prevention and control, including linkage to appropriate COVID-19 care. We will conduct programmatic evaluation of routine data collected by PSI and implementing partners to provide analysis of time trends and possible contribution of COVID-19 Ag-RDT provider-delivered testing. PSI will implement the testing and facilitate linkage to care and treatment and will collect programmatic data.

## **Activities**

### **Epidemiological**

A structured questionnaire (CP01) shall be used to collect data on the participants' socio-demographic characteristics, assess for COVID-19 symptoms, willingness to test and follow next steps on COVID-19 prevention if positive.

### **Qualitative**

A subsample of 20 participants will be selected, 5 per outreach site, to ascertain the acceptability of the use-case in line with Proctor's implementation outcomes (Client SSI).

Study coordinators and 2 study providers will be interviewed to write up the TIDieR description for this use-case, as well as to input into the acceptability of the use-case in line with Proctor's implementation outcomes (Provider SSI topic guide & CK01).

#### Cost and cost effectiveness

A subsample of 20 participants will be selected to receive a structured questionnaire asking clients about the time spent testing, and any costs incurred in accessing COVID-19 testing (Patient cost questionnaire\_Final).

A maximum of 12 providers shall also be interviewed and observed through a time and motion approach, ascertaining the costs of overhead supplies (utilities, facility supervision, administrative, cleaning, security and transport costs), COVID-19 testing costs (Ag RDT or PCR), assessing rooms, equipment, furniture, staffing, consumables and equipment used for each COVID-19 testing service, and time and motion (method of collecting cost data) for staff providing COVID-19 testing services (Provider costing data collection tool).

#### Sample size considerations

We conservatively assume that 70% of participants the targeted outreach settings will accept to be tested for COVID-19. For the sample proportion to be estimated to within  $\pm 0.05$  (5%) using the 95% confidence level, a sample of 323 participants would be required.

In all congregate settings we will aim to recruit for research every 2nd eligible person aiming to stop when the overall sample size of 323 is reached.

#### Recruitment process

Below are the steps to be followed before, during and after screening for eligibility in congregate settings by the study team. Upon notification of a COVID-19 case at any of the selected congregate settings either via PSI or directly or via any other media, the project coordinator will contact the leadership of the institution.

Once confirmed and authorized the study team will then visit the institution within at most a day after being given a go ahead by the leadership of the institution. All available occupants of the congregate institution present at the time will then be screened for eligibility.

Before commencing any data collection, all eligible individuals at the institution will be provided information sheets to read followed by informed consent process completed by a research assistant.

Potential participants who may require more time will be allowed to read information sheets with potential participation on the next day following consent. The project coordinator who is medically trained will be available onsite to answer any clinical questions. Any prospective participant who declines to participate in the study will not be punished and such a decision will not be passed onto any of the institution. Additionally, for prospective participants who decline to participate but show COVID-19 symptoms will be encouraged to be tested through the existing government COVID-19 testing sites.

#### Inclusion criteria for people in populated settings

Residents of heavily populated environments shall be eligible to participate if they are:

1. Aged 18 years and above

2. Students/employees or residents of the institution or community where an outbreak is being investigated
3. Well enough to complete study activities
4. Willing and able to provide informed consent (written/thumbprint/verbal)

### **Exclusion criteria for people in populated settings**

Residents of heavily populated environments shall be ineligible to participate if they:

1. Have tested positive for COVID-19 and are still within the isolation period
2. Have a medical contraindication to nasal swabs (e.g. bleeding disorders, recent facial trauma).
3. Are unable to provide informed consent

### **Main analysis**

Descriptive analysis of the proportion of participants and binomial exact 95% CI accepting to test, testing positive and accepting next steps for COVID-19. The proportions will be stratified and compared either using t-test or Chi-square test for continuous and categorical variables accordingly.

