### **Sample size**

We conservatively assume that 70% of participants across clinics will accept to be tested for COVID-19. For the sample proportion to be estimated to within  $\pm 0.05$  (5%) using the 95% confidence level, a sample of 323 participants would be required.

However, we assume the following:

- i. Integration of COVID-19 testing into routine health services will be maintained for the foreseeable future but will target people with symptoms of COVID-19 and for those who are at high risk for severe COVID-19.
- ii. We also assume, based on precedent, that low proportions will test positive outside of an epidemic wave, with each epidemic wave lasting 6 weeks, and we expect 2 waves within the study period.
- iii. We assume that each facility serves at least 100 OPD attendees per day, of whom at least 30% will have one or more COVID-19 symptoms, and that 70% of those eligible will accept SARS-CoV-2 testing i.e., 21 attendees could accept testing per day over 12 sites, totaling a potential study population of 252 in any one day, or 7,560 per 6week wave.

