### **Sample size**

The number of contacts will be determined by the number of index cases and is not known at the time of design. However, assuming 2% of all our screening tests from the above use cases are positive i.e., ~30,000 overall tests, then about 600 index cases will be generated. Assuming there would be three household contacts and 2 two close contacts, then a total of 3000 contacts will be approached. When oral antivirals become available in Malawi, information on treatment eligibility and how to access antivirals will be included.

For statistical power with the secondary distribution of self-test kits, we assume 60% of contacts will be willing to self-test for COVID-19 if offered. For the sample proportion to be estimated to within  $\pm 0.05$  (5%) using the 95% confidence level, a sample of 370 contacts accepting self-tests is required.

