### **5.10.2. Statistical analysis**

Analyses will use R(35) and Stata 14.0 (Stata Corp, Texas, USA). Baseline characteristics will be computed as proportions or median (interquartile range [IQR]) as appropriate. Estimates such as proportions and mean will be reported along with 95% confidence intervals (CI). Regression analysis: logistic for binary outcomes and linear for the turn-around-time or any other continuous outcome will be explored.

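### The ±5-point precision and exact binomial intervals for congregate settings (at most 5 sites) and outpatients (12 clinics) ignore clustering by site

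*Protocol*

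**What the plan says.** **Congregate settings (Protocol 5.1.3).** The primary outcome is the proportion accepting a test. The sample size paragraph states: "We conservatively assume that 70% of participants the targeted outreach settings will accept to be tested for COVID-19". From this it derives 323 people for ±0.05 at 95% confidence. The Overview says: "We will select at most 5 congregate settings aiming to offer screening to ~323 participants". Recruitment takes every second eligible person, "aiming to stop when the overall sample size of 323 is reached". The Main analysis reports the "proportion of participants and binomial exact 95% CI accepting to test, testing positive and accepting next steps for COVID-19", with strata compared by t-test or chi-square.

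**Outpatients (Protocol 5.1.2).** The same 323 is derived from the same assumption, "We conservatively assume that 70% of participants across clinics will accept to be tested for COVID-19", with recruitment at the 12 facilities of the health care worker study. The Main analysis repeats the exact binomial wording and the same tests.

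**Contacts (Protocol 5.1.4).** The assumption is that "we assume 60% of contacts will be willing to self-test for COVID-19 if offered", and "a sample of 370 contacts accepting self-tests is required". The Main analysis lists percentages and counts, calls itself exploratory and names no interval. Section 5.10.2 promises 95% confidence intervals in general terms.

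Section 5.8 repeats the sizes, with 369 in place of 370. No design effect or ICC value appears anywhere; the term ICC stands only in the acronym list. Overdispersion between facilities is addressed only for the health care worker primary outcome (5.1.1, Main analysis).

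**The concern.** People in one university, workplace or clinic share an outbreak, a gatekeeper, a testing team and local attitudes, so acceptance is likely to vary between sites by more than binomial chance. With few sites, that between-site variation dominates the uncertainty, and recruiting more people within a site hardly reduces it. An exact binomial interval does not see it.

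The estimates are meant to travel. The Executive summary says that the results will inform Ministry of Health scale-up plans, and section 2.7 says that lessons will be passed to national providers. An interval that reads as ±5 points but carries the information of far fewer independent people would give policy makers false assurance about uptake elsewhere.

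The interval method is named in the protocol, so this is not detail left to an analysis plan. A plan that followed the protocol faithfully would carry the fault forward.

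**Working it through.** **Inputs from the protocol.** Acceptance p = 0.70 and n = 323 for congregate and outpatient; p = 0.60 and n = 370 for contacts; half-width d = 0.05 at 95% confidence. Clusters: at most 5 settings (323/5 = 64.6 people each), 12 clinics (323/12 = 26.9 each), and 5 contacts per index case (three household plus two close, 5.1.4).

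**Assumed, not in the documents.** The ICC, and equal cluster sizes. Unequal sizes would make the results worse.

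**Step 1: reproduce the stated sizes.** n = 1.96² × p(1−p)/d².
- p = 0.70: 322.7, so 323.
- p = 0.60: 368.8, so 369 (stated as 369 or 370).

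The sizes match with a design effect of exactly 1. The exact binomial interval at 226/323 runs from 64.6% to 74.9%, or ±5.1 points.

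**Step 2: allow for clustering.** Design effect DE = 1 + (m−1) × ICC; half-width = c × √(p(1−p) × DE/n), with c = 1.96 or the t quantile on clusters minus 1 df. Coverage of the unadjusted interval is about 2Φ(1.96/√DE) − 1.

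Example, congregate at ICC 0.05: DE = 1 + 63.6 × 0.05 = 4.18; √(0.21 × 4.18/323) = 0.0521. Multiplying by 1.96 gives ±10.2 points; multiplying by 2.776 (t, 4 df) gives ±14.5.

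Congregate, 5 settings:

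| ICC | DE | Effective n | ± points (1.96) | ± points (t, 4 df) | Coverage of nominal 95% |
|---|---|---|---|---|---|
| 0.01 | 1.64 | 197 | 6.4 | 9.1 | 87% |
| 0.02 | 2.27 | 142 | 7.5 | 10.7 | 81% |
| 0.05 | 4.18 | 77 | 10.2 | 14.5 | 66% |
| 0.10 | 7.36 | 44 | 13.6 | 19.2 | 53% |

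Outpatients, 12 clinics:

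| ICC | DE | Effective n | ± points (1.96) | ± points (t, 11 df) | Coverage of nominal 95% |
|---|---|---|---|---|---|
| 0.01 | 1.26 | 257 | 5.6 | 6.3 | 92% |
| 0.02 | 1.52 | 213 | 6.2 | 6.9 | 89% |
| 0.05 | 2.30 | 141 | 7.6 | 8.5 | 80% |
| 0.10 | 3.59 | 90 | 9.5 | 10.6 | 70% |

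Part of the t-based widening reflects only the small number of sites: with 5 settings and ICC 0 it is already ±7.1 points.

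**Step 3: could more people restore ±5?** As n grows without limit, the half-width tends to 1.96 × √(p(1−p) × ICC/k) for k sites. With 5 settings this floor is ±4.0 points at ICC 0.01 and ±5.7 at 0.02. So ±5 needs about 901 people at ICC 0.01 and cannot be reached at 0.02 or above. With t on 4 df the floor at ICC 0.01 is 2.776 × √(0.21 × 0.01/5) = ±5.7, so ±5 is out of reach even there. With 12 clinics, using 1.96, ±5 needs 437 people at ICC 0.01 and 685 at 0.02, and is out of reach at 0.05.

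**Step 4: contacts, n = 370, 5 per index case.** ICC 0.05/0.10/0.20/0.30 gives DE 1.2/1.4/1.8/2.2 and ±5.5/5.9/6.7/7.4 points. At the 3000 contacts the protocol expects, even ICC 1 (DE = 5) gives 1.96 × √(0.24 × 5/3000) = ±3.9 points.

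**The case against.** **Descriptive aims and fixed sites.** Table 1 labels the outpatient and congregate components descriptive process evaluations, and the 12 clinics are named. If the target is acceptance at exactly those sites, the binomial interval is adequate. That is correct as far as it goes, but it does not fit the stated use of the results for national scale-up, and no passage restricts the inference to the sampled sites.

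**The ICC is not in the documents.** This stands: no single figure can be asserted. At ICC 0.01 to 0.02 the outpatient loss is small. The congregate loss is material even at the low end, because there are at most 5 sites.

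**Stronger readings that the documents do not support.**
- A reader might infer that intervals for contacts are also far too narrow. Section 5.1.4 names no exact binomial interval, and Table 1 calls 370 a minimum. Read literally, 370 acceptors imply about 370/0.60 = 617 contacts offered kits, in which case ±5 holds up to an ICC of about 0.17.
- A reader might infer that the health care worker secondary comparisons (days off, linkage, knowledge) will ignore facility and so inflate type I error. The t-test and chi-square sentence belongs to the outpatient and congregate sections. The general sentence in 5.10.2, "logistic for binary outcomes and linear for the turn-around-time or any other continuous outcome will be explored", prescribes no arm contrast and does not say how facility is handled. That may be settled in an analysis plan.
- A reader might infer that one large university will fill the sample. The stopping rule sets no per-setting limit, but every-second-person selection applies in all settings, and Table 3 plans interviews at four locations. Dominance by one site is possible, not planned.

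**Conclusion.** The point holds for congregate settings and, less severely, for outpatients. The sample sizes reproduce only under independence, and the named interval assumes it too. Over assumed ICCs of 0.01 to 0.10, the properly based half-width is about 1.3 to 2.7 times the stated one for congregate settings and 1.1 to 1.9 times for outpatients, using 1.96 throughout. Intervals on t with the available degrees of freedom are wider still.

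The conclusion rests on three assumptions: an ICC in that range, roughly equal site sizes, and inference to settings and clinics beyond those sampled. Five settings is also the favourable case. With four equal settings, ICC 0.05 gives ±11.2 points using 1.96, or ±18.1 using t on 3 df.

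For contacts the only fault is that the minimum of 370 ignores clustering by index case, and the expected numbers would absorb it.

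**What to change.** 1. **5.1.2 and 5.1.3, Main analysis.** Replace the exact binomial interval with one computed from site-level proportions, or a cluster-robust interval, using t on sites minus 1 df. Apply the same clustering to the t-test and chi-square comparisons of strata.
2. **Sample size paragraphs of 5.1.2 and 5.1.3, and section 5.8.** State an assumed ICC and the resulting precision on the same t basis, in place of ±5%. A range taken from the tables above would serve. Do not quote 1.96-based precision alongside a t-based interval.
3. **5.1.4.** Cluster the interval on index case. The single aggregate record per index case already allows this. Note that 370 gives about ±5.5 to ±7.4 points at ICC 0.05 to 0.30, and that the expected 3000 contacts would still meet ±5.
4. **No fixed cap of 65 per setting.** It is a tempting safeguard, but it reaches 323 only if all five settings are used; four would give 4 × 65 = 260. Reporting the number recruited and the acceptance proportion for each setting shows any imbalance without endangering the target.

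The cost is a wider stated precision and slightly more analysis work. No extra participants are needed. If inference is meant to stop at the sampled sites, the protocol can say so and keep the binomial interval, but the results could then not be presented as estimates for other settings.

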### **Ethical considerations for outbreak investigation use case**

Eligible participants will be given detailed information about the study and will be invited to participate (NC08B). Written informed consent will be obtained before study procedures commences. Written informed consent also explicitly covers the potential for subsampling for the process evaluation explaining that clients may be selected to be asked some additional questions about their experiences of the testing which means that the interviews could take up to 1hour.

In addition, written informed consent will be obtained from participants subsampled to take part in the patient cost exercise (NC09), as well as written informed consent from the providers sampled to take part in the provider cost exercise (NC10). If participants are illiterate, participant information sheets will be read to participants and thumbprint consent, alongside witness signature will be taken.

Written informed consent will also be obtained from the study providers for the 2 qualitative interviews (NC03).

#### **5.1.4. Secondary distribution of self-test kits**

##### **Objectives:**

To evaluate the acceptability of unsupervised self-testing provided through secondary distribution of COVID-19 Ag-RDT self-test kits to contacts of patients testing positive for COVID-19.

##### **Outcome:**

Proportion of contacts accepting the offer of COVID-19 self-testing from the index client.

Secondary outcomes include an assessment of risk factors of the contacts including vaccination history, and socio-demographics.

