|                                             |                                                          |                                                                                   | iii. Sub-sample participant cost interviews, and provider cost observations establishing cost of process                                                                                                                                                                      |                                                                                                                                                                                                                                                                                                                                                           |                  |
| 4. Secondary distribution of self-test kits | Self-testing:
Demonstration project evaluation | Proportion of contacts self-tested for COVID19 (contact uptake of self-test kits) | i. Epi interviews establishing participant sociodemographic profiles
ii. Sub-sample qualitative interviews establishing acceptability of demonstration model
iii. Sub-sample participant cost interviews establishing cost of model ( no provider observations ) | Any positive participant from the use-cases.
All eligibility assessed
i. All receive baseline epi interview, and telephone follow up after 14 days
ii. subsample of 20 qualitative interviews
iii. subsample of 20 patient-level costing interviews

Minimum requirement of 370 contacts to ascertain uptake i | 6,000 self-tests |

|  |  |  |  |  |
|--|--|--|--|--|
|  |  |  |  |  |
|  |  |  |  |  |
|  |  |  |  |  |
|  |  |  |  |  |
|  |  |  |  |  |
|  |  |  |  |  |
|  |  |  |  |  |
|  |  |  |  |  |

MLW: Malawi Liverpool Wellcome Trust Clinical Research Programme; PSI: Population Services International

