### **Main analysis**

The main analysis relates to exploratory analysis of acceptability (% eligible who accept the offer of secondary distribution of kits to household or other close contacts) and contact acceptability (% contacts who self-test), safety (self-report of any social harms experience by the index patient), numbers of kits distributed, numbers of contacts accepting kits, number of contacts testing at least once, number of contacts with positive immediate or day 5 results, and number of contacts diagnosed within 5 days of symptom onset including asymptomatic contacts.

Qualitative data analysis will be captured by semi-structured interview during which index patients will also be asked about any perceived benefits and regrets, and their willingness to recommend secondary distribution to others testing positive for COVID-19.

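### The secondary distribution component defines its main outcome in two ways (offer accepted, or self-tested) and states its 370 as acceptors when the calculation gives contacts offered; the practical effect is modest

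*Protocol*

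**What the plan says.** The component's main outcome appears in three places in the protocol.

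- Section 5.1.4, Outcome: "Proportion of contacts accepting the offer of COVID-19 self-testing from the index client". It is listed ahead of the secondary outcomes.
- Section 5.1, Table 1, main outcome column for use case 4: "Proportion of contacts self-tested for COVID19 (contact uptake of self-test kits".
- Section 5.1.4, Main analysis: "contact acceptability (% contacts who self-test". The same paragraph lists "numbers of contacts accepting kits, number of contacts testing at least once" as separate counts. It adds an index-level measure (the percentage "eligible who accept the offer of secondary distribution of kits to household or other close contacts") and opens with "The main analysis relates to exploratory analysis of acceptability". It does not say which measure leads.

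The size appears in four places.

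- Section 5.1.4, Sample size: "a sample of 370 contacts accepting self-tests is required". The basis is 60% of contacts willing to self-test if offered, a margin of 0.05 and 95% confidence.
- Table 1: "Minimum requirement of 370 contacts to ascertain uptake".
- Executive summary: 370 participants.
- Section 5.8: 369 participants.

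**The concern.** Accepting an offer and carrying out the test are different events, since a kit can be taken and left unused. The Outcome subsection and Table 1 therefore name different main results for the same component. Sections 2.7 and 5.1.4 present this work as evidence on whether contacts could be offered self-tests instead of all being presumed positive. For that decision, the share of contacts who tested and the share who said yes answer different questions.

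The size statement has a related fault. A precision calculation for a proportion gives the number of people over whom the proportion is taken. Section 5.1.4 attaches that number to those who accept, which is the numerator. Read literally, it sets a different recruitment target and a different precision from the one stated beside it.

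**Working it through.** **Inputs.** From section 5.1.4, Sample size: p = 0.60 of contacts willing to self-test if offered, d = 0.05, 95% confidence (z = 1.96), and 600 index cases with 5 contacts each, so 3000 contacts approached.

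**1. Reproduce the plan's figure.** n = z² × p(1 − p) / d² = 1.96² × 0.24 / 0.0025 = 368.8, rounded up to 369. This agrees with section 5.8, and 370 is the same figure rounded. In this formula n is the denominator, that is, contacts offered a test.

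**2. 370 read as contacts offered (Table 1).** Half-width = 1.96 × √(0.24 / 370) = 0.0499, which is the stated 5 points. Expected acceptors: 370 × 0.60 = 222.

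**3. 370 read as acceptors (section 5.1.4).** Contacts to be offered: 370 / 0.60 = 616.7, so 617. Half-width = 1.96 × √(0.24 / 617) = 0.0387. The gap between readings is 617 − 370 = 247 contacts. At 5 contacts per index case this is 370 / 5 = 74 index cases against 617 / 5 = 123.4, so 124. Only the denominator reading matches the stated margin.

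**4. Compare with expected numbers.** 370 and 617 are both well below 3000, and 74 and 124 are both well below 600.

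**5. Are the two outcomes the same thing in different words?** The main analysis lists contacts accepting kits and contacts testing at least once as separate items. Section 5.1.4, Recruitment process, asks separately whether kits were delivered and whether they were used. Section 5.5 costs kits distributed and kits used separately. The two proportions are equal only if every accepting contact tests.

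**6. How far apart could they be?** The documents give no rate of use among acceptors. As an illustration only, assume 60% accept and 50% to 90% of those test. The self-tested proportion is then 0.60 × 0.50 = 0.30 to 0.60 × 0.90 = 0.54, against 0.60 for acceptance. Both the use rate and the reading of the protocol's 60% as acceptance are assumptions here.

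**The case against.** The strongest reply is that little hangs on this. The component is a demonstration project with no comparator, hypothesis test or success threshold, and its analysis is labelled exploratory. The main analysis already commits to reporting both testing and kit acceptance. The documents also lean one way: Table 1 and the main analysis both use self-tested, so the Outcome subsection looks like the outlier, and its phrase about accepting the offer of self-testing may be loose wording for the same thing. On size, Table 1 calls 370 a minimum and all consenting index cases are enrolled, so 370 is not a stopping rule. A target of 370 acceptors would in any case be more precise than required.

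Most of this stands, and it limits the consequence. It does not remove the inconsistency. The main analysis separates acceptance from testing, so a reader cannot safely treat the Outcome wording as a synonym, and nothing ranks the measures.

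A reader might go further and infer that the headline could be picked once the data are in. The documents do not support that as a finding. Both quantities are named in advance and would be reported together, and no threshold rewards choosing one. Nor do they support a specific drop from 60% to 30–54%, since the protocol gives no use rate and its 60% is willingness to self-test if offered, not kit acceptance.

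**Conclusion.** The point holds as an inconsistency to be corrected, with modest practical effect. The main outcome has two different numerators in the current text. The size in section 5.1.4 is misstated: 369 or 370 is right as contacts offered and wrong as contacts accepting, which would imply about 617 offered and a margin of 3.9 points. Precision and feasibility are not threatened on the protocol's own expectation of about 3000 contacts. These figures rest on the protocol's 60%, on its 5 contacts per index case, and on the simple binomial formula that reproduces its sample size.

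**What to change.** Use one main outcome in Table 1 and in the Outcome and Main analysis subsections of 5.1.4: contacts who self-tested at least once, divided by contacts offered a self-test. This keeps the numerator already used in two of the three places. The denominator matches the 60% assumption, which applies to contacts if offered, and the aggregate record in 5.1.4, Recruitment process, already includes the number offered. Report kit acceptance, and the proportion self-tested among all listed adult contacts, as secondary. Listed contacts should not be the main denominator without revisiting the 60%, because some listed contacts may never receive the offer.

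In 5.1.4, Sample size, state the requirement as 370 contacts offered self-testing, and align the Executive summary, Table 1 and section 5.8 to the same unit and to one of 369 or 370.

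The cost is wording only. The follow-up described in 5.1.4 and section 6.2 covers numbers offered, kit use and numbers tested, although the questionnaire itself is not among the pages available. The downside is that the headline figure may be lower than acceptance would have been.
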